### 2.5. Stage 2: Qualitative Study

#### 2.5.1. Sample

To obtain as much information as possible from the interviews, maximum difference sampling will be used. The SCAD patients included in the quantitative study as the target population, and as far as possible, SCAD patients with different levels of SDM participation, with different risk factors for cardiovascular disease, with different ages, with different levels of education, and with different economic statuses representative of the results of the quantitative study will be selected for the interviews. The final sample size will be determined according to the information saturation; that is, the interview will end when no new content and themes emerge, and 10–20 interviewees are expected to be included.

#### 2.5.2. Study Setting and Procedure

(1)The researcher will contact potential interviewees in advance to arrange suitable times and locations for the qualitative interviews. The research will employ face-to-face semi-structured interviews conducted by the same researcher who will undergo comprehensive training in qualitative research methodology. The researcher will engage with the interviewees through a question-and-answer format following the structure of the interview outline. Based on the interviewees’ responses, the order of the outline will be adapted and follow-up questions will be posed to gather as much rich information as possible.(2)The interview outline of this study is developed based on the theory of planned behavior and relevant literature and will be revised according to the survey results of the quantitative stage. Prior to the formal interviews, two respondents who meet the inclusion criteria will be pre-interviewed. Based on the results of these pre-interviews, the formal interview outline will be revised and finalized, and the interviewing techniques will be improved.(3)Before the interview, the researcher will prepare the interview outline, informed consent form, writing implement, interview transcript, and notebook, and adjust the audio recording equipment. At the outset of the interview, the researcher will elucidate the purpose and content of the interview, as well as the rationale for recording, and obtain the interviewee’s signature on the informed consent form, indicating their understanding and consent. The location of the interview will be selected with the intention of providing the interviewees with a setting that will be convenient, comfortable, and relaxed. The primary locations selected for the interviews in this study will be quiet wards, conference rooms, and disposal rooms.(4)During the interview process, the researcher will additionally record the interviewees’ expressions, emotional responses, body movements, and other non-verbal behaviors. After the interview, a diary will be written in a timely manner to document the researcher’s impressions and facilitate data analysis.(5)According to the principle of data saturation in qualitative research, the interview will be concluded when the researcher cannot extract new themes and content from the interview data.

#### 2.5.3. Instruments

Semi-structured Interview Outline (Table 2).

The interview outline of this study is developed based on the theory of planned behavior and relevant literature, and will be revised according to the survey results of the quantitative stage.

#### 2.5.4. Data Analysis

The qualitative data analysis will be performed using thematic coding methods. The interview recording will be transcribed word for word within 24 h after the end of the interview, and the recording will be repeatedly listened to to ensure the accuracy of the transcribed content, and the interviewees’ modal words and other content will be supplemented with the interview record form. The transcribed text is then imported into the Nvivo12.0 software for management, encoding, and analysis. The transcription and analysis of the data will be carried out independently by two researchers, and consensus will be reached through discussion and the questioning of a third researcher in the case of disagreement.

### 2.6. Integration Study

In order to comprehensively analyze the results of the quantitative and qualitative studies, we will integrate the quantitative and qualitative results through a joint display [36] in a mixed methods approach using TPB as a framework. We will combine the current status and factors influencing the participation of SCAD patients in SDM in the quantitative study and the themes, sub-themes, and related results extracted from the qualitative study, and present them together visually so that we can compare the findings of the different methods and analyze them comprehensively. Figure 3 presents the Gantt chart illustrating the timeline for the mixed method study.

### 2.7. Patient and Public Involvement

Patients and the public were not directly engaged in the development process of the protocol.

## 3. Discussion

### 3.1. Strengths

The study employs a mixed method approach with an explanatory sequential design, incorporating both qualitative and quantitative methods, to comprehensively understand the factors that influence SCAD patients’ participation in SDM. The SCAD patients who report low, moderate, and high levels of participation in SDM and have different demographic and clinical characteristics will be purposively selected to be interviewed to understand their different experiences and explore their promoting and hindering factors. Furthermore, these findings can provide a reference for the design of future intervention studies, as well as provide healthcare providers with targeted information and communication to help SCAD patients make the most appropriate decisions.

Cost–benefit analysis (CBA) and expected utility maximization (EUM) are widely recognized as rational criteria [37]. However, TPB provides an additional perspective as a rational criterion. Firstly, TPB emphasizes understanding and predicting human behavior by focusing on intentions, attitudes, subjective norms, and perceived behavioral control [23]. This makes it particularly useful for interventions to change specific behaviors, like health-related practices [23]. This will have significant implications for our subsequent intervention studies. This can be more actionable than the more abstract calculations of CBA and EUM, which might not always translate directly into practical strategies.

Secondly, unlike CBA and EUM, which primarily consider economic outcomes and individual preferences, TPB incorporates social and psychological factors. It acknowledges that people’s behaviors are influenced by their beliefs about what others think they should do (subjective norms) and their perceived ability to perform the behavior (perceived behavioral control) [38].

Finally, in the SDM process, patients’ attitudes toward the different treatment options are crucial. If a patient has a positive attitude toward a particular treatment because they believe it will lead to better health outcomes, they are more likely to consider and choose that option during the decision-making process. SDM allows these attitudes to be explicitly discussed and considered [23]. From the results, the outcome of SDM is a shared decision that ideally reflects a strong intention to follow the agreed-upon treatment plan. Because the decision is made collaboratively and fully considering the patient’s views and perceived control, it is more likely that the patient will follow through with the treatment, which is consistent with the TPB’s emphasis on the link between intention and behavior.

### 3.2. Limitations

Firstly, our study participants will be recruited using convenience sampling from just one clinical setting. The single setting and the sampling methodology are non-probabilistic, limiting the findings’ generalizability. Secondly, for the elderly with lower levels of education, there is a possibility that they may not be able to comprehend the content of the questionnaires and interview outlines, which could potentially lead to communication difficulties. It is incumbent upon the researcher to elucidate the questionnaire and interview outline to the elderly in simple and clear statements. This may require a greater investment of time and energy on the part of the patient, which could potentially impede the research process.

TPB also has some limitations that should be mentioned. Firstly, TPB assumes that individuals make decisions based on the rational assessments of available information. In reality, however, people often make decisions based on past behavior and habits, which are not fully captured by the theory [39]. This may lead to overestimating the predictive power of attitudes, subjective norms, and perceived behavioral control in some situations. Secondly, TPB assumes that individuals have a degree of control over their behavior. However, in some cases, people may have limited control due to factors such as their medical condition, mental health problems, or environmental constraints. When patients lack control over their behavior, TPB’s predictive power is reduced because intentions may not be translated into action [39].

### 3.3. Dissemination

The corresponding results and conclusions will be disseminated in correlative conferences and journals after the completion of the study, and data pertinent to this study’s results will be freely available from the corresponding author via reasonable request. Furthermore, we will disseminate and share the findings with the public and relevant health administration organizations. This may prompt discourse surrounding patient participation in SMD and potentially shape patients’ understanding and attitudes towards SMD, thereby enhancing the actual level of patient involvement in SMD and benefiting patients.

## 4. Conclusions

SDM fosters an equitable partnership whereby both the healthcare provider and the patient collectively assume responsibility for making medical decisions. An explanatory sequential mixed methods design will be used to explore the study aims. The results will provide an in-depth analysis of the factors that influence SCAD patients’ participation in SDM and their participation experiences, revealing their unique clinical challenges and providing valuable insights. These findings aim to strengthen communication between healthcare providers and patients with SCAD, and provide targeted recommendations and references for clinical improvement and the promotion of SCAD patients’ participation in SDM. However, there are some limitations in the design and theory of this study, which can be discussed in future studies.

## Figures and Tables

**Figure 1 healthcare-12-01883-f001:**
[figure not shown]
The theory of planned behavior.

**Figure 2 healthcare-12-01883-f002:**
[figure not shown]
Flow chart of the mixed method study.

**Figure 3 healthcare-12-01883-f003:**
[figure not shown]
Gantt chart for this mixed method study.

**Table 1 healthcare-12-01883-t001:** Statistical test information table.

Statistical Test Information Table			
Num	Tests	Variables	Type of Information
1	descriptive statistics	demographic and clinical characteristics, participation in SDM, patient attitudes, decision self-efficacy, intention, and social support	Frequency, percentage; Mean ± SD or M (P_25_, P_75_) (normality or not)
2	monofactor analysis	sex, BMI, ethnicity, place of residence, working conditions, medical payment method, stent implantation or not, and the first time to be hospitalized for SCAD or not	Mann–Whitney U-tests
		age, marital status, education level, average annual household income, drinking status, smoking status, duration of illness, severity of angina, and number of diseased coronary arteries	multi-sample rank-sum tests
3	multiple logistic regression analyses	Variables that are statistically significant after monofactor analysis	independent variables
		participation in SDM	dependent variable
4	Spearman correlation analysis	participation in SDM (Single dimension)	
		patient attitudes (Single dimension)	
		decision self-efficacy (Single dimension)	
		intention (Single dimension)	
		social support (friends support, family support, and significant other support)	

Demographic and clinical characteristics: sex, BMI, ethnicity, place of residence, working conditions, medical payment method, stent implantation or not, and the first time to be hospitalized for SCAD or not; age, marital status, education level, average annual household income, drinking status, smoking status, duration of illness, severity of angina, and number of diseased coronary arteries.

**Table 2 healthcare-12-01883-t002:** Semi-structured Interview Outline.

Opening remarks	I appreciate your interest in this study. I will ask you some questions about your involvement in SDM during this hospitalization. Your responses will be recorded, but your identity will remain confidential.	
SDM Participatory experience	1. Can you recall when the most impressive/recent medical decision was made during your hospitalization? 2. Please describe in detail what was the decision-making process? (Decision on what? How did you participate in the decision? How was the decision made?) ① What actions did you take before making the decision? ② How did you make the decision when the real decision was made? (Please describe in detail) ③ After making the decision, reviewing the whole process, what do you think about the decision-making process?	
Participation in SDM Impact Factors	Intention	① How would you like to be involved in decision-making during your hospitalization? Why do you wish to participate in decision making in this way? ② What do you think led to your willingness to participate in shared decision-making being consistent/inconsistent with your actual behavior in decision-making participation?
	Attitude	① What is your attitude towards participation in shared decision-making? Why do you think so? ② What do you think are the advantages and disadvantages of participating in shared decision-making for you? What are the effects? (For you? Your children? Your family? Others?) ③ How do you feel about your decision-making participation behavior in this way? (Please describe in detail)
	Subjective Norm	①What influence does your partner/family/friends/healthcare provider/other individuals or groups have on your participation in SDM/taking this decision-making participatory behavior? Why did/didn’t it have an impact?
	Perceived behavioral control	① How confident are you in participating in SDM? What would affect your confidence in participating in SDM? ② What aspects of your confidence/non-confidence/competence do you think have led to your decision-making participation behavior in this way? (Please describe in detail)
	Other factors	① What other factors do you think cause/hinder your participation in sharing decisions? ② What other factors do you think may have caused/hindered you from making other decision-making participation behaviors?
Closing remarks	1. Is there anything you would like to share or add about today’s interview?	

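### Interview outline (Table 2): the opening remark, one probe and all three experience sub-probes assume the patient took part or decided, and SDM is not defined

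*Protocol article*

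**What the plan says.** Section 2.5.1 samples interviewees for maximum difference, with level of SDM participation among the criteria. Section 3.1 confirms that all three levels are wanted: "The SCAD patients who report low, moderate, and high levels of participation in SDM" are to be selected, with the aim of finding what promotes and what hinders participation.

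Table 2 prints the outline. It opens with "I will ask you some questions about your involvement in SDM during this hospitalization". The experience block then runs as follows:

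- Question 1: "Can you recall when the most impressive/recent medical decision was made during your hospitalization"
- Question 2: a request to describe the decision-making process, with the probes "Decision on what? How did you participate in the decision? How was the decision made"
- Sub-probe ①: "What actions did you take before making the decision"
- Sub-probe ②: "How did you make the decision when the real decision was made"
- Sub-probe ③: "After making the decision, reviewing the whole process, what do you think about the decision-making process"

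The items on intention, attitude, subjective norm and perceived behavioral control follow, including "How confident are you in participating in SDM". Sections 2.5.2 and 2.5.3 say that the outline will be revised in the light of the survey results. Section 2.5.2 adds two pre-interviews, after which the outline is finalized.

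**The concern.** A question that takes participation for granted invites the respondent to describe participation. A patient whose physician decided is asked what they did before deciding, how they decided, and what they think having decided. That patient must either correct the interviewer or fit the account to the question. Sub-probe ② also sits awkwardly with SDM itself, which the Introduction describes as a responsibility held jointly by patient and provider: it presents the patient as sole decider.

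The second part is comprehension. The outline asks for attitudes to SDM and confidence in it without saying in ordinary words what it is.

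At stake is the quality of the accounts from patients who took little or no part. Those accounts bear directly on the hindering factors that the study sets out to find. Section 2.6 then compares the interview findings with the survey findings, so leading prompts could blur that comparison.

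**Working it through.** No arithmetic model applies. The check is a reading of every prompt in Table 2 against the sampling, eligibility and procedure sections.

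**1. Who may be interviewed.** Interviewees come from the survey sample (Section 2.5.1). Section 2.4.1 excludes patients who handed the decision entirely to family. It does not exclude patients whose physician decided. The Introduction leads one to expect such patients: in one cited study of patients undergoing percutaneous coronary intervention, 16% were asked about their treatment preferences.

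**2. Classification of the experience prompts.**

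| Prompt | Assumes the patient took part or decided? |
|---|---|
| Question 1 | No; passive wording |
| Question 2, stem | No |
| Question 2, probe on what was decided | No |
| Question 2, probe on how the patient participated | Yes, participation |
| Question 2, probe on how the decision was made | No; passive wording |
| Sub-probe ① | Yes, decision |
| Sub-probe ② | Yes, decision |
| Sub-probe ③ | Yes, decision (in its opening clause) |

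Count: 1 probe + 3 sub-probes = 4 leading prompts out of 8. All 3 numbered sub-probes are among them. The opening remark, outside this block, also assumes involvement.

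**3. Later items.** The intention item allows that wish and behavior may differ. The norm item asks why others did or did not have an influence. One control item covers both confidence and lack of it. The last block asks what causes or hinders participation. These can be answered by someone who took no part.

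**4. Definition of the term.** The abbreviation appears in the opening remark, the subjective norm item and the perceived behavioral control items. The full term appears in the intention and attitude items. Definitions in Table 2: 0.

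**5. Whether the stated safeguards remove the problem.**

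- Explaining the interview's purpose and content at the start (Section 2.5.2) does not commit the interviewer to defining SDM.
- Explaining the outline simply to elderly patients (Section 3.2) covers one subgroup, and plain language does not remove a false premise.
- Reordering and follow-up questions (Section 2.5.2) leave the correction to the interviewer's improvisation.
- The two pre-interviewees need only meet the inclusion criteria (Section 2.5.2), so neither need be a low participator.
- Revision after the survey and the pre-interviews is planned, but not for this purpose.

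**The case against.** The strongest reply is that this is a draft topic guide for a trained interviewer, not a fixed questionnaire. Half the experience prompts are neutral, and a patient can answer the probe on how the decision was made by saying that the doctor decided. The intention item already asks how the patient would have liked to be involved and why. Low participation is a band of 0–33 on a 0–100 scale, so it does not mean none. The clearest family-decided cases are excluded. Interviewees have already completed the SDM questionnaires. The article prints English, and the words spoken to Chinese-speaking patients are not shown, so one cannot say that they hear an unexplained abbreviation.

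Most of this stands, and it rules out stronger readings. A reader might infer that the outline tells every interviewee that they made the decision, or that the whole experience block presupposes it; the count above shows otherwise. A reader might infer that low participators cannot answer; the neutral and two-sided items show that they can. A reader might also infer that the term is never explained; that is true of the printed outline only, since oral explanation is foreseen.

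The reply does not remove the printed wording. The defect lies in questions that are given in full, not in detail left to a longer document, and no safeguard commits to changing them.

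**Conclusion.** The point holds as a wording defect of limited size. The opening remark and four of eight experience prompts, including all three numbered sub-probes, are leading for patients whose physician decided, and the outline defines neither SDM nor its full form.

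How many interviews this touches cannot be read from the protocol. If the expected 10–20 interviewees were spread evenly over three levels, which is an assumption, the low group would number 10/3 ≈ 3.3 to 20/3 ≈ 6.7, or about 3–7. Patients who took no part may be only some of these.

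Two further inferences are not supported. The protocol does not single out low participators as the group that matters most; they are one of three levels within a maximum-difference sample. Nor does anything show that the joint display would mistake an effect of wording for a real disagreement between methods; that is possible, not demonstrated. No stated figure or quantitative analysis changes. This is a nearly free improvement, not a threat to the study.

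**What to change.** Change Table 2 as follows:

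- **Opening remark:** announce questions about how decisions on the patient's treatment were made during the stay, whoever made them.
- **Question 2 and its sub-probes:** ask who was involved and what each person did, what part, if any, the patient had, who made the final choice, and how the patient now views the way it was decided. Keep the neutral prompts.
- **Follow-up for patients who took no part:** ask why, and whether they had wanted to.
- **Definition:** read one plain-language sentence explaining shared decision making before the attitude and confidence items, in the language of the interview.
- **Pre-interviews:** where feasible, hold one of the two with a patient whose SDM-Q-9 level is low.

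The cost is rewording the outline before the pre-interviews. No extra staff, visits or interviews are needed.

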## Data Availability

Any data generated from this study will be available for sharing upon the submission of a request to the primary investigator of this study.
